### Participant withdrawal

Participants in the study are free to withdraw from participating at any point, without giving a reason and without their legal rights or usual care being impacted. It is possible for a participant to with draw from receiving the therapy, but continue to remain in the trial for the follow up assessments, in essence, participants will be asked if they are willing to continue data collection assessments at 16 weeks and 28 weeks, if they wish to withdraw from the iMAPS intervention. While being reminded of their right to withdraw without giving a reason, we will politely ask if they are willing to give a reason, but remind them that this is entirely voluntary.

If continued participation for some reason is assessed by the researchers to be harmful in some way, then we may withdraw a participant. The Trial Steering Committee (TSC) which incorporates a Data Monitoring and Ethics function will review all instances of adverse events, regardless of whether they are judged to be attributable to the trial or interventions. Reviewing this information, the independent committee members will decide if a participant should be withdrawn from the study. All adverse events deemed related to study participation will be reported the Research Ethics Committee (See Section 9 for further details).

There is a possibility that individuals taking part may lose capacity to consent to continue participating in the study. In this event, we would pause their participation to see if they regain their capacity (acknowledging that capacity fluctuates in people with psychosis and may be temporary). However, if they continue to lack capacity, this may also mean they are no longer able to consent to ongoing participation in the study or for their data to be retained. In line with previous studies (including the iMAPS case series) we will seek informed consent in advance from all participants to retain their data if they subsequently withdraw because of loss of contact or are withdrawn by the study team due to loss of capacity

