**Full Trial Progression Criteria:**

We will progress to a full trial if we all our criteria below are classed as GREEN; if one or more is AMBER, we will investigate whether it is possible to make adjustments to the trial design to overcome any problems and, if that appears possible, progress to a full trial (including an assessment of the success of our adjustments in its internal pilot, where appropriate); if one or more is RED, we will not progress unless we can make the substantial amendments which would be necessary to make a full trial feasible.

1. Recruitment: GREEN: >=80% (n>=36) of target recruited; AMBER >=40 % (n=18-35)-< 80% of target recruited; RED <40% (n<18) of target recruited.
2. Retention: GREEN: >=80% of participants providing 16-week outcome data ; AMBER: >60%- <80% of

participants providing 16-week outcome data; RED: <60% of participants providing 16-week outcome data.

- 1. Adherence: GREEN>=75% adherence of participants attend at least 5 sessions of therapy, AMBER>=40% participants

attend at least 5 sessions of therapy; RED: <40% of participants attend at least 5 sessions of therapy (based on Jolley et al. 2015).

Assessment Measures

|  | **Procedures and Questionnaires** | **Mins** | **Baseline** | **16 Weeks Follow Up** | **28 Weeks Follow Up** |
| --- | --- | --- | --- | --- | --- |
|  | Demographics | 5 | X | As needed | As needed |
| **Psychosis Measures** | PANSS | 60 | X | X | X |
|  | PSYRATS | 15 | X | X | X |
|  | QPR | 5 | X | X | X |
| **Imagery** | Brief Imagery Interview  Visual Analogue Scales/MIPQ  Psychosis Imagery Questionnaire (PIQ) | 10  5 | X  X | X | X |
| **Schemas** | BCSS | 2 | X | X | X |
| **Trauma** | TALE | 5 | X |  |  |
|  | ITQ | 5 | X | X | X |
|  | BES | 5 | X | X | X |
| **Mental Health and Functioning** | BAI | 5 | X | X | X |
|  | CDS | 9 | X | X | X |
|  | WEMWBS | 5 | X | X | X |
|  | PSP | 10 | X | X | X |
| **Health Economics** | EQ-5D-5L | 2 | X | X | X |
|  | ReQoL-10 | 2 | X | X | X |
|  | Economic Patient Questionnaire | 10 | X | X | X |
|  |  |  |  |  |  |
| **Working Alliance** | WAI-client | 5 | 3^rd^ Session | 6^th^ | 9^th^ |
|  |  | 5 |  |  |  |
| **THERAPIST ONLY** | WAI-therapist | 5 | 3^rd^ Session | 6^th^ | 9^th^ |
|  | iMAPS therapy fidelity Checklist  CTS-R or CTS-Psy |  | A selection of therapy sessions will rated in supervision and by an independent external therapist |  |  |
| **Adverse Effects** | CGI-IP | 1 | Each Session |  |  |
|  | CGI-SP | 1 | Each Session |  |  |

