## ADVERSE EVENTS

***Definitions***

| **Term** | **Definition** |
| --- | --- |
| **Adverse Event (AE)** | Any untoward medical occurrence in a participant to whom psychological therapy/assessment or qualitative interview has been administered.  Non severe adverse events will be defined as a score of >3 (Agree quite a lot or a lot) on any item of the participant rated 26 item Adverse Events of Psychotherapy Questionnaire (AEP; Hutton, 2016; Pyle et al 2016) which is given to participants on either completion of therapy, or if they have given informed consent, sent to those who drop out or end therapy early. |
| **Adverse Reaction (AR)** | An untoward and unintended response in a participant to a psychological therapy/assessment or qualitative interview which is related to the therapy/assessment or interview administered to that participant.  The phrase "response to a psychological therapy/assessment or qualitative interview" means that a causal relationship between a trial therapy/assessment or interview and an AE is at least a reasonable possibility, i.e. the relationship cannot be ruled out.  All cases judged by either the reporting clinically qualified professional or the Chief Investigator (acting on behalf of the Sponsor) as having a reasonable suspected causal relationship to the psychological therapy/assessment or qualitative interview qualify as adverse reactions. |

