| **Serious Adverse Event (SAE)** | A serious adverse event is any untoward medical occurrence that:   - results in death - is life-threatening - requires inpatient hospitalisation or prolongation of existing hospitalisation - results in persistent or significant disability/incapacity - consists of a congenital anomaly or birth defect   Other ‘important medical events’ may also be considered serious if they jeopardise the participant or require an intervention to prevent one of the above consequences.  NOTE: The term "life-threatening" in the definition of "serious" refers to an event in which the participant was at risk of death at the time of the event; it does not refer to an event which hypothetically might have caused death if it were more severe.  In line with an approach previously used (Pyle et al 2016) which was adapted from Klingberg et al 2012), in addition we will define serious adverse events as:   1. death by suicide 2. suicide attempt 3. suicidal crisis without attempt (rating 2 on item 8 of Calgary Depression Rating Scale for Schizophrenia CDSS) 4. severe symptoms increase (rating of > 6 on the patient or researcher rated CGI and CGI-I). |
| **Serious Adverse Reaction (SAR)** | An adverse event that is both serious and, in the opinion of the reporting Investigator, believed with reasonable probability to be due to the psychological therapy/assessment or qualitative interview, based on the information provided. |
| **Related and Unexpected Serious Adverse Reaction** | A serious adverse reaction, the nature or severity of which is not consistent with the effects or consequences of a psychological intervention. |

NB: to avoid confusion or misunderstanding of the difference between the terms “serious” and “severe”, the following note of clarification is provided: “Severe” is often used to describe intensity of a specific event, which may be of relatively minor clinical significance. “Seriousness” is the regulatory definition supplied above.

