**AEs that do not require reporting**

Any untoward medical occurrence that is **not** related to the psychological therapy/assessment or qualitative interview that has been administered.

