**SAEs**

All SAEs **related** to the psychological therapy/assessment or qualitative interview occurring between baseline until end of study must be recorded on the SAE report form and emailed to Sponsor immediately and within 24 hours of the research staff becoming aware of the event. Refer to the SAE form for the information that will be collected for all SAEs.

Any change of condition or other follow-up information should be emailed to the Sponsor as soon as it is available or at least within 24 hours of the information becoming available. Events will be followed up until the event has resolved or a final outcome has been reached.

| **Email completed all SAEs FAO:**  [**[contact]**](mailto:[contact])  [**[contact]**](mailto:[contact]) |
| --- |

SAEs must be followed-up until resolution and sites must provide follow-up SAE reports if the SAE had not resolved at the time the initial report was submitted.

On receipt of the SAE Report Form, the Sponsor will send an acknowledgement of the SAE. This acknowledgement will include an SAE reference number which should be included on all future correspondence regarding the SAE.

The SAE Report Form will be reviewed by the CI for assessment of causality. If the SAE is related to the psychological therapy/assessment or qualitative interview, the CI will review the expectedness in relation to the nature or severity of an event which is not consistent with the effects or consequences of a psychological intervention. In the case that the SAE is related and **unexpected**, the study team will submit a report to REC, HRA and the Sponsor within the expedited timeframes.

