## Harms

The number of safety events (e.g., AEs and SAEs) and number (and proportion) of participants reporting at least one safety event will be summarised by treatment arm. Summary measures will be number (%).

Safety events will also be tabulated by:

- Death by suicide
- Suicide attempt
- Suicidal crisis without attempt (rating 2 on item 8 of Calgary Depression Rating Scale for Schizophrenia CDSS)
- Severe symptoms increase (rating of > 6 on the patient or researcher rated CGI and CGI-I)

They will be reported by both overall and by treatment arm.

Treatment effects will be estimated by the difference in event rates and 95% CI for the differences.

In addition, we will tabulate and present frequencies of the endorsed individual items in the Adverse Effects in Psychotherapy (AEP) scale (29) for those participants allocated to the intervention arm. This is a self-report measure of potential adverse effects completed by the participants at the end of therapy assessment measuring 7 broad categories: worsening difficulties, poor engagement (including low motivation), situational change, no benefit from therapy, stigma, conflict with others (family, care team) and feeling better.

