|  | Median(IQR) | 13.5 (7.0 to 17.0) | 16.0 (12.0 to 19.0) | 14.0 (12.0 to 17.0) | 0.0 (0.0 to 12.0) | 12.0 (5.0 to 20.0) | 5.0 (0.0 to 12.0) |
|  | Missing | 0 | 0 | 0 | 1 | 0 | 1 |

**Supplementary Table 4d: Post Hoc Analysis Treatment effects at 16 weeks of the Psychotic Symptom Rating Scales (PSYRATS) for those participants with auditory hallucinations & delusions at baseline**

|  | **Scale range** | **N** | **Effect estimate** | **in favour of …** | **95% CI** | **90% CI** | **85% CI** | **80% CI** | **75% CI** | **SD_pooled_** | **SES (95%CI)** |
| --- | --- | --- | --- | --- | --- | --- | --- | --- | --- | --- | --- |
| **Psychotic Symptom Rating Scales (PSYRATS)** | |  |  |  |  |  |  |  |  |  |  |
| Auditory Hallucinations Subscale (AHS) | 0-44 | 17 | -3.4 | iMAPs | (-17.4 to 10.6) | (-15.1 to 8.3) | (-13.1 to 6.4) | (-12.5 to 5.7) | (-11.4 to 4.7) | 13.9 | -0.2 (-1.2 to 0.8) |
| Delusions Subscale (DS) | 0-24 | 17 | 1.3 | TAU | (-3.3 to 6.0) | (-2.5 to 5.2) | (-2.2 to 4.9) | (-1.8 to 4.4) | (-1.5 to 4.2) | 5.8 | 0.2 (-0.6 to 1.0) |

*Effect estimate = iMAPS intervention+TAU - TAU*

*Standardised effect size (SES)=* *Effect estimate /* SD_pooled_; the corresponding 95%CI is calculated by dividing the limits of the 95%CI for the effect estimate by the SD_pooled_.

**Supplementary Table 5: Response rates as measured by the Positive and Negative Syndrome Scale (PANSS) by treatment allocated and time point.**

|  | **N (%)** | | | |
| --- | --- | --- | --- | --- |
|  | **16 Weeks** | | **28 Weeks** | |
|  | **iMAPs** | **TAU** | **iMAPs** | **TAU** |
| **Improvement category** | **n=25** | **n=11** | **n=18** | **n=8** |
| Deterioration or no change | 8 (32) | 5 (45) | 8 (44) | 2 (25) |
| >0% but <25% reduction from baseline | 7 (28) | 3 (27) | 4 (22) | 1 (13) |
| 25% to <50% reduction from baseline | 6 (24) | 3 (27) | 2 (11) | 1 (13) |
| 50% to <75% reduction from baseline | 2 (8) | 0 (0) | 1 (6) | 1 (13) |
| 75% to <100% reduction from baseline | 0 (0) | 0 (0) | 1 (6) | 0 (0) |
| Missing | 2 (8) | 0 (0) | 2 (11) | 3 (38) |

**Supplementary Table 6:** Number of Adverse Events and Serious Adverse Events by Treatment Group and Overall

|  | **iMAPS + TAU** | **TAU** | **Overall** |
| --- | --- | --- | --- |
| **Unrelated** |  |  |  |
| Total Serious Adverse Events (SAE), n  Hospital Admission  Physical  Mental Health/Psychiatric  Suicide Attempts | 1  1  0 | 0  0  0 | 2 |
| Total Adverse Events (AE), n  Suicidal Ideation with a plan | 8 | 3 | 11 |

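### Protocol 3.18 records only related adverse events, and harms are checked more often in the therapy arm, so the between-arm comparison in SHEAP 7.6 needs one recording and ascertainment rule for both arms

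*Combined protocol and SAP*

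**What the plan says.** **Analysis.** SHEAP 7.6 summarises events, and participants with at least one event, by arm. It asks for four named categories and then states: "Treatment effects will be estimated by the difference in event rates and 95% CI for the differences". It has no relatedness restriction, and SHEAP 5.3 makes all randomised participants the safety population.

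**Recording.** Protocol 3.18 has AEs recorded when they are related to therapy, assessment or qualitative interview. Unrelated occurrences fall under the heading "AEs that do not require reporting". SAEs related "to the psychological therapy/assessment or qualitative interview occurring between baseline until end of study must be recorded on the SAE report form"; the Chief Investigator then assesses causality from that form.

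**Oversight.** Under Protocol 3.6.1 the TSC "will review all instances of adverse events, regardless of whether they are judged to be attributable to the trial or interventions". Section 4.10.1 sends SAEs to the TSC together with the decisions on whether they were attributable.

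**Definitions and schedule.**
- Protocol 3.17 defines a non-severe AE as a score above 3 "on any item of the participant rated 26 item Adverse Events of Psychotherapy Questionnaire" (AEP). The AEP is given at the end of therapy or, with consent, after early exit from it.
- The SAE list in 3.17 includes "suicidal crisis without attempt (rating 2 on item 8 of Calgary Depression Rating Scale for Schizophrenia CDSS" and a severe symptom increase on the CGI.
- The assessment table in 3.11 lists "CGI-IP | 1 | Each Session" and shows no 16- or 28-week CGI. The depression scale (CDS/CDSS) is scheduled at baseline, 16 and 28 weeks in both arms.
- Section 3.17 also has blinded research assistants complete the harms protocol at end of treatment and follow-up, with clinicians repeating it at each therapy session.

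**Results table.** Supplementary Table 6 carries, as non-serious AEs, "Suicidal Ideation with a plan | 8 | 3 | 11" (iMAPS+TAU, TAU, overall).

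**The concern.** A randomised harms comparison is useful because it does not depend on attributing single events: an excess in one arm shows even if nobody linked any one event to therapy. A rule that filters on relatedness before recording gives that up. It also tilts the comparison, because therapy-related events can occur in one arm only.

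The second problem is unequal opportunity for detection. Events found through the AEP, or through session CGI and clinician checks, come from therapy contact. If they enter a rate difference, part of that difference measures how often people were asked.

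The third is narrower. Any high AEP item counts as an AE, yet SHEAP 7.6 lists feeling better among the AEP categories.

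At stake are how far the reported safety contrast can be interpreted, and wording that a definitive trial might reuse.

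**Working it through.** **1. Reproduce Table 6.** iMAPS+TAU: 2 SAEs + 8 AEs = 10. TAU: 0 + 3 = 3. Overall: 2 + 11 = 13. All are in the unrelated panel; the related panel is zero throughout. The totals agree. The plan states no precision target for harms.

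**2. Effect of the recording rule.** The denominators are 31 and 14 (Supplementary Table 2). Table 6 counts events, not participants, so I assume that each event is a different person. SHEAP 7.6 names no interval method, so two are shown. With d = p1 − p2 and Wilson limits l, u for each arm:
- Newcombe: d − √[(p1−l1)² + (u2−p2)²] to d + √[(u1−p1)² + (p2−l2)²].
- Wald: d ± 1.96 √[p1(1−p1)/n1 + p2(1−p2)/n2].

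| Events counted | iMAPS+TAU | TAU | d (points) | Newcombe 95% CI | Wald 95% CI |
|---|---|---|---|---|---|
| Related only (3.18 read literally) | 0/31 | 0/14 | 0.0 | −21.5 to +11.0 | 0 to 0 |
| All events | 10/31 = 32.3% | 3/14 = 21.4% | +10.8 | −18.7 to +33.2 | −16.2 to +37.9 |
| SAEs as tabulated | 2/31 = 6.5% | 0/14 | +6.5 | −15.6 to +20.7 | −2.2 to +15.1 |

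In the first row the Wilson upper limit is z²/(n+z²), that is 3.84/34.84 = 11.0% and 3.84/17.84 = 21.5%. The Wald interval collapses to zero width.

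**3. Effect of unequal ascertainment.** A full course gives 12 session checks + 2 scheduled visits = 14 occasions, against 2 in TAU. At the adherence threshold of 5 sessions it is 5 + 2 = 7. Assume equal true risk, independent occasions and detection probability p per occasion (illustrative; the documents give none). Then P(at least one detected event) = 1 − (1−p)^k:

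| p | iMAPS, k = 14 | iMAPS, k = 7 | TAU, k = 2 |
|---|---|---|---|
| 1% | 13% | 7% | 2% |
| 2% | 25% | 13% | 4% |
| 5% | 51% | 30% | 10% |

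The AEP is not counted here. It adds a further opportunity in iMAPS with no TAU counterpart.

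**4. AEP definition.** Section 3.17 sets no restriction on which items count. SHEAP 7.6 names seven categories, one of them feeling better. Read literally, strong agreement with such an item is an AE. The items and their scoring are not in the documents, so this needs checking against the instrument.

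**5. Table 6 against SHEAP 7.6.** The plan asks for death by suicide, suicide attempt, suicidal crisis without attempt, and severe symptom increase. Table 6 as printed has a row for attempts, but none for the other three.

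**The case against.** The strongest reply is that the wording of 3.18 did not govern what happened. Assessing causality after the SAE form is filed presupposes forms for unrelated events. Sections 3.6.1 and 4.10.1 expect unrelated events to reach the TSC, and Table 6 reports unrelated events from both arms. *Related* also covers assessments and interviews, which TAU participants undergo. This stands: a reader might infer that the comparison is empty, and the documents do not support that. What remains is contradictory text. Because that text excused staff from recording unrelated events, the documents cannot show that such events were captured equally in both arms.

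On ascertainment, blinded assistants complete the harms protocol in both arms, the CGI trigger may be researcher-rated, session checks are described as serving clinical care, and SHEAP 7.6 already tabulates the AEP for the intervention arm only. This also stands in part: there is a common basis for a fair contrast. SHEAP 7.6 does not confine the rate difference to it, and 3.17 still makes high AEP scores count as AEs.

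Other inferences go too far:
- *The plan dropped the suicidal-crisis category.* It is in 3.17 and SHEAP 7.6, and the CDS is scheduled in both arms. It is missing only from Table 6.
- *There were 13 SAEs, not 2.* That requires all 11 suicidal-ideation-with-plan events to meet the CDSS item 8 criterion. The documents never equate the two, so 2 to 13 is the logical range and not an estimate.
- *The comparison decides go or no-go.* The progression criteria are recruitment, retention and adherence, and SHEAP 4.6 sets no formal statistical stopping criteria.
- *Relatedness was judged unblinded.* The documents do not say, and they provide for independent TSC review of attribution decisions.

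**Conclusion.** The point holds as a moderate issue. Protocol 3.18 contradicts 3.6.1, 4.10.1, its own causality step, SHEAP 5.3 and SHEAP 7.6. Applied to the reported data it would remove all 13 events and turn 10 v 3 into 0 v 0.

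Separately, a rate difference over all events is biased towards more events in iMAPS. The size of that bias cannot be estimated from the documents; the illustration shows only that it could be large if session-detected events are counted. The literal AEP reading is a point to check, with no demonstrated effect on results. Whether any of the 11 ideation events meet the SAE definition in 3.17 cannot be determined.

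With 31 v 14 participants the intervals are wide under any rule. The correction removes a source of bias and does not add precision.

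**What to change.** 1. Reword Protocol 3.18 so that every AE and SAE is recorded in both arms, with relatedness as an attribute, consistent with 3.6.1 and 4.10.1.
2. In SHEAP 7.6, limit the rate difference and its interval to events ascertained the same way in both arms, whatever their relatedness. Examples are deaths, suicide attempts, admissions, and CDSS item 8 at the 16- and 28-week visits, each from a source used identically in both arms.
3. Report AEP-defined AEs and session-detected events descriptively for iMAPS only.
4. Check the AEP items and exclude any that describe benefit from the AE definition in 3.17.
5. Reconcile Table 6 with 3.17 and SHEAP 7.6: check the 11 events against the SAE definition and add the planned rows, including zero rows.

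**Cost.** Wording changes, re-tabulation and slightly more event recording; Table 6 shows that unrelated events were already being recorded. The CDS and service use, including admissions, are already collected in both arms. The price is fewer event types in the formal contrast.

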## Blinding

To reduce detection bias, researchers undertaking assessments will be blind to the allocation. The success or otherwise of our attempts at blinding will be recorded. Where a research assistant is unblinded, another research assistant will make an appointment to undertake the assessment.

*Allocation concealment (from both recruiting staff member and [potential] participant) will be ensured, as the system will not release the randomisation code until the participant has been randomised which takes place after all baseline measurements have been completed*.

.

It is not anticipated that un-blinding of the research assistants will occur in the trial and it is not expected that there would be any reason for emergency un-blinding of the researchers. Any instances of unintentional un-blinding will be recorded.

The Trial Statistician will remain blinded to treatment allocation until after the Statistical Analysis Plan (SAP) have been sign off and the analysis of unblinded data commences.

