## FOLLOW UP ASSESSMENTS

Participants who are randomised will be invited to complete a follow up assessment at 16 weeks (end of therapy assessment) and again at 28 weeks (follow up assessment).

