Our iMAgery focused therapy for Psychosis approach has previously been tested in a case series and no severe adverse events were reported. Building on work by others in psychological treatments for psychosis, we wish to carefully record and report adverse events of psychological interventions and wish to implement a protocol developed assessing and managing any such risk, which will be completed at end of treatment and at follow up by research assistants who are blind to the allocated group. We are adding the use of the CGI and additional criteria below.

This protocol will also be completed by clinicians during the intervention, that is each session, to complete an assessment of severe adverse events, for clinical purposes.

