## Timing of outcome assessments

Outcome assessments will be performed at baseline, 16 weeks (end-of-therapy assessment) and 28 weeks (follow-up assessment) although there is no strict window for outcome assessments.

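### The SHEAP times the therapy-arm-only AEP questionnaire at the 16-week visit run by blinded assessors, the protocol ties it to the end of therapy, and neither says how it is kept from the assessor

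*Combined protocol and SAP*

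**What the plan says.** **SHEAP 7.6 (Harms)** presents AEP item frequencies "for those participants allocated to the intervention arm" and describes the form thus: "This is a self-report measure of potential adverse effects completed by the participants at the end of therapy assessment".

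**SHEAP 4.8** lists the follow-up visits as "16 weeks (end-of-therapy assessment) and 28 weeks (follow-up assessment"). **Protocol 3.12** does the same: "a follow up assessment at 16 weeks (end of therapy assessment) and again at 28 weeks (follow up assessment").

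**Protocol 3.3** has a research assistant conduct these visits, covering both the interview and the self-report measures. Protocol 3.10 and the SHEAP section on blinding require those assessors to be blind. Protocol 3.10 adds a remedy: "Where a research assistant is unblinded, another research assistant will make an appointment to undertake the assessment".

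**Protocol 3.17 (definitions)** gives a different occasion for the AEP: "which is given to participants on either completion of therapy, or if they have given informed consent, sent to those who drop out". Participants who stop therapy before its planned finish are covered in the same way. The AEP row of the schedule in protocol 3.11 likewise speaks of the end of therapy or drop-out, with consent to sending obtained beforehand.

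**Protocol 3.17 (text after the definitions)** describes a protocol for adverse-event risk, "which will be completed at end of treatment and at follow up by research assistants who are blind to the allocated group". That sentence does not name the AEP.

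**The concern.** The AEP asks about harms of psychotherapy, so only participants who had therapy have reason to complete it. A form of this kind, handled at a blinded visit, tells the assessor the arm. The SHEAP places it at exactly such a visit, and no section puts a barrier between the form and the assessor.

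Participants cannot be blinded, as the SHEAP acknowledges, so assessor blinding is the stated protection against detection bias. It matters most for PANSS and PSYRATS, which protocol 3.11 has the research assistants administer by interview and which are two of the four candidate primary outcomes in SHEAP 7.2 (with QPR and BCSS). CDSS and PSP are also rater-scored.

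The exposure is one-sided, because only the iMAPS arm would have the form. Unblinding is also a feasibility outcome (protocol 3.11) and is reported by randomised group (SHEAP 7.5). Breaks produced by the plan's own paperwork would be counted there and could mislead the design of the definitive trial.

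**Working it through.** No figure in the plan bears on this point, so the check sets the text side by side and then sizes the exposure.

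**Step 1. When and by whom**

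| Question | SHEAP | Protocol |
|---|---|---|
| Which arm? | 7.6: tabulated for the intervention arm only | 3.17: given on completing or leaving therapy |
| When? | 7.6: at the end-of-therapy assessment | 3.17 and 3.11 schedule: at completion of therapy, or sent after drop-out |
| What is the end-of-therapy assessment? | 4.8: the 16-week visit | 3.12: the 16-week visit |
| Who runs that visit? | Blinding section: blinded researchers | 3.3 and 3.10: a research assistant, blind |
| Who issues, collects and enters the AEP? | Not stated | Not stated |

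The SHEAP's restriction to the intervention arm governs a tabulation. That only this arm receives the form follows from protocol 3.17, which ties it to therapy.

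The two occasions are not the same date. Protocol 3.16 gives a twelve-week therapy phase and the visit is at week 16, so for therapy finished on schedule the gap is roughly 16 − 12 = 4 weeks.

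**Step 2. Other routes to the assessor**

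- Protocol 3.26: when follow-up is remote, the research assistant fills in the paper measures from the participant's answers. An AEP collected that way would be read by the assessor.
- Protocol 3.26 and 3.28: a researcher enters all data, and other assistants check them. Even a form issued by the therapist could reach an assessor, since no access restriction is written.

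**Step 3. How many at 16 weeks**

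Inputs are the column headings of Supplementary Tables 4a and 5, taken as participants seen: iMAPS 31 randomised, 25 at 16 weeks; usual care 14 randomised, 11 at 16 weeks.

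- SHEAP 7.6 followed literally: at most 25/31 = 81% of iMAPS participants, and 0 of 11 usual-care participants, revealed by receiving the form. The other 31 − 25 = 6 were not seen at that visit.
- Protocol 3.17 followed with therapist or postal handling, and forms kept from assessors: possibly 0.

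The range is therefore 0 to 25. An assessor who knew the rule could also infer usual care from the absence of a form.

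**Step 4. Which ratings**

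No order within the visit is specified, and protocol 3.11.1 allows an assessment to be split over two or more meetings. If the AEP preceded the interviews, the 16-week PANSS and PSYRATS would be exposed. If it came last, those ratings would already be made and the exposure would move to later ratings by the same assessor.

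At 28 weeks, 18 iMAPS participants were seen. The tables do not say how many of them were among the 25 seen at 16 weeks: the overlap is at least 25 + 18 − 31 = 12 and at most 18. How many would have been rated by an assessor who had handled their AEP cannot be fixed from the documents.

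**The case against.** The strongest reply is that the SHEAP sentence introduces a table and is not an instruction to sites. Sites work from the protocol, which ties the form to completion of therapy or sending. The form is self-report, and nowhere is the blinded assessor told to give it, see it or collect it. This stands as far as it goes: unblinding is a foreseeable risk, not a necessary result. It does not remove the conflict, because the SHEAP uses a name that both documents attach to the 16-week visit, and the protocol does not say who handles the form.

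Three further points stand.

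- The blinded adverse-event assessment in protocol 3.17 does not name the AEP. The next paragraph has clinicians complete the same protocol at each session, so it cannot simply be the AEP. It is not evidence that blinded assistants administer the form, although it should say so.
- The AEP entry's place under the 16-week column proves little. In the same schedule, the working-alliance and CGI rows use the visit columns for therapy sessions.
- Unblinding is recorded and reported by arm, so an imbalance would be visible. That detects the problem but does not prevent it.

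A reader might infer that every iMAPS participant is unblinded, or that all 18 iMAPS ratings at 28 weeks are compromised. The documents support neither: non-attenders are not seen, those who stop early may be sent the form, and the overlap between visits is not given. A reader might also infer that replacing an assessor would itself disclose the arm. Supplementary Table 12 records research assistants leaving and being replaced, so a change of assessor need not signal allocation.

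**Conclusion.** The point holds as a conflict between documents and a missing safeguard. SHEAP 7.6 and protocol 3.17 give different occasions for an arm-identifying form. The SHEAP's occasion is a blinded visit, and no text keeps the form from assessors at the visit, at data entry or at checking.

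The size is 0 to 25 of 31 iMAPS participants revealed by this form at 16 weeks, against none in usual care. The upper end assumes that the AEP is done at the visit for everyone seen and that the assessor sees it. The lower end assumes therapist or postal handling with no later access by assessors. Whether the 16-week or only later ratings are affected depends on an order that is not stated. The documents do not show that unblinding by this route occurred.

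Recruitment is complete, so the point now bears on how the reported blinding breaks are read and on the definitive-trial protocol. Because the exposure would be differential and the remedy is cheap, the sponsor should act on it.

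**What to change.** Reconcile SHEAP 7.6 with protocol 3.17 and the AEP row of the schedule in 3.11 so that all three give one occasion. Then state that:

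- the AEP is issued and returned through the therapist, an existing unblinded team member or post, and is not part of the 16-week research assessment;
- assessors do not hand out, collect, enter or check it until their 28-week ratings are complete;
- the blinded adverse-event assessment in protocol 3.17 does not include the AEP.

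For this trial's report, state how the AEP was actually handled, so that recorded blinding breaks can be interpreted.

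The cost is wording in the protocol and SHEAP, with no new staff role. The downside is that some forms may be lost compared with completion at a visit.
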